### Outline of the study procedure for patients

For all patients starting with cardiovascular or oral blood glucose-lowering medication with a first prescription from a DOH GP, the GP starts a treatment plan in the electronic patient information system that the GPs and pharmacies use in their current daily practice. Then, the following process starts when the patient comes to the pharmacy for the first dispense.On first dispensing at the pharmacy, when the pharmacist considers the patient eligible for participation, the patient receives a short oral introduction to the study and an invitation to participate in the study.When the patient is interested in participation, the pharmacist asks for the patient’s permission to send the patient an email with a link to the study survey and collects the patient’s Citizen Service Number (CSN). Additionally, the pharmacist makes an appointment for the second dispense.The pharmacist (assistant) uses a tablet/web browser to register the patient for potential enrollment in the study.One week after the pharmacy visit, the computer system sends an email to the patient containing the link to the questionnaire.Then, the patient receives a paper-based package of study information and consent form to take home. This information will be provided on top of the usual information given during the first dispense in the pharmacy and will not replace any information that is usually provided during the first dispense.At home, the patient reads the study information and decides on participation. If the patient decides to participate, (s)he answers the link in the email received and completes the survey. The answers are used to produce a profile, which is sent to the electronic patient file system so that the pharmacists of the intervention practices have it available during the second dispensing appointment when the intervention starts (For control patients, the profile is only made available after completion of the study). The survey answers are retained until the end of the study.The patient sends the signed informed consent forms by regular mail in a pre-stamped envelope.For the second dispensing at the pharmacy, the pharmacists in the control arm do not receive the results of the medication adherence assessment from their patients, and they provide usual care. This includes the usual information at the start of a new drug as described in the guidelines of the pharmacists’ profession (KNMP richtlijn ‘ter hand stellen’, http://www.knmp.nl/praktijkvoering/bekostiging/begeleidingsgesprek-nieuw-geneesmiddel/knmp-richtlijn-ter-hand-stellen-juni-2013).The pharmacist in the intervention group checks whether the patient has completed the medication adherence assessment and takes care to provide a second dispensing of the drug.If the patient has not completed the assessment at the moment of the second dispensing, the patient is asked whether (s)he would like to participate and is asked to complete the survey in the pharmacy on a tablet.

Patients that prefer to participate with a paper-based questionnaire instead of an online questionnaire can sign and send in the paper informed consent form and indicate their preference. They will receive the questionnaire per regular mail together with a return envelope. Those participants that fill out a paper-based questionnaire return the questionnaire by regular mail, and their data will be entered into the system by a research worker. As an alternative, participants who prefer the online questionnaire but do not have access to a computer or Internet at home can fill out the questionnaire at the pharmacy during their visit for the second dispensing.

At the second dispensing moment, pharmacists in the intervention group will initiate a tailored intervention for patients with an increased risk for nonadherence. The intervention will be tailored to the patient’s emotional, cognitive, and practical barriers, as identified by the barriers assessment. Patients without an increased risk for nonadherence, receive usual care (delivery of medication only). As mentioned above, the ProMAS scores and profiles will be stored in the electronic patient information system.

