**Methods/design:**

In a cluster-randomized controlled trial 25 pharmacies in the Netherlands will be randomized to the intervention or control arm. Patients registered in a general practice participating in a collaborative can be included when they start cardiovascular or oral blood glucose-lowering medication prescribed by their general practitioner.

Participants complete an assessment consisting of measuring nonadherence risk and potential barriers to adherence. For patients with an increased nonadherence risk, a graphic barrier profile is created, showing to what extent eight cognitive, emotional, or practical barriers are present.

All patients will fill in the medication-adherence assessment twice: between 1 and 2 weeks after the start of the medication and after 8 months.

The intervention strategy consists of discussing this barrier profile to overcome barriers. Pharmacists and assistants of the intervention pharmacies are trained in discussing the profile and to offer a tailored intervention to overcome barriers. In the control arm, patients receive care as usual.

The primary outcome is medication-adherence of patients with a high risk of nonadherence at 8 months follow-up.

Secondary outcomes include the difference in the percentage of patients with an increased nonadherence risk between intervention and control group after 8 months, the predictive values of the baseline questionnaire in the control group in relation to medication-adherence after 8 months, medication-adherence after 1 year follow-up, and barriers and facilitators in the implementation of the tool.

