#### Pharmacies

The DOH cooperates closely with a number of community pharmacies (so-called CaZo cooperation). In total, 25 pharmacies have joined the cooperative. A representative of DOH will contact all 25 pharmacies connected to the DOH cooperation and provide them an invitation and an information leaflet about the study. Three members of the research team will visit all pharmacists who express their intention to participate. After a detailed explanation of the study aims, methods, and expected outcomes to the pharmacists, written informed consent for both participation and collection of de-identified patient data from the pharmacist’s database will be obtained.

The participating pharmacies are randomized for the intervention or control group, which implies that the patients are clustered within pharmacies. Pharmacies are stratified into small or large depending on their number of patients registered with DOH GPs. After the randomization procedure (drawing from a hat by an independent research assistant and consecutive allocation) has been performed, the pharmacies will be informed of their assignment to either the intervention group or the control group. Only pharmacists and pharmacy assistants from the intervention group are being trained to interpret the barriers to adherence profile and to provide tailored care. This prevents contamination between the intervention and control patients. Because patients in the Netherlands predominantly visit one pharmacy for all their medication, pharmacists are assumed to have complete medication dispensing information for their patients [13].

Due to the test of the medication-adherence tool, both pilot pharmacies will have to participate in the intervention group.

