### Implementation of the medication-adherence tool

To deliver the tailored intervention, training on a patient-centered communication technique will be offered to the pharmacists, and one of the pharmacy assistants of the pharmacies assigned to the intervention group. Intervention pharmacists and their pharmacy assistants will receive a three-hour training session before starting the trial, consisting of a brief introduction to the proposed communication technique, demonstration of a second dispense moment with a barrier profile, and skills practice using role play. The pharmacists and pharmacy assistants will be specifically instructed on discussing the profile with the patients in order to offer a tailored intervention to overcome cognitive, emotional, or practical barriers.

Intervention pharmacies will also receive a manual containing instructions for discussing and overcoming the various potential barriers for medication adherence. In this manual, potential barriers are categorized into cognitive, emotional and practical nonadherence barriers. Furthermore, intervention pharmacies will receive a follow-up group session from the trainer on the patient-centered communication technique to provide support and exchange experiences on discussing the barrier profiles. In addition, three members of the research team will visit all participating pharmacists. At least the pharmacist and one experienced pharmacy assistant of a pharmacy will be present during that appointment. We will explain the study in detail and provide them with an easy-to-understand explanation of the workflow concept and subsequently discuss how the workflow concept can be optimally tailored to existing routine work procedures in the pharmacy. One of the researchers will be available during working hours to answer questions arising from the study. Finally, pharmacists will be offered the opportunity to contact one of the pilot pharmacists to ask questions and advices about the study procedures. Table 3 summarizes the various elements of the implementation strategy.

**Table 3 Tab3:** Elements of the implementation strategy

*■* Visit of the pharmacy by the research team to provide the manual and to tailor the workflow concept to existing work procedures in an optimal way
*■* Training session for pharmacists on patient-centered communication, using the manual and discussing the barrier profile
*■* Follow-up group session of the trainer on discussing the barrier profile

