### Outcomes

The primary outcomes are as follows:The primary outcome is the difference in the medication adherence of patients with an initial high risk of nonadherence between the intervention and the control group, measured by pharmacy dispensing records at 8 months follow-up.

The secondary outcomes are as follows:Based on data from all patients participating:The difference in the percentage of patients with an increased risk for nonadherence based on the ProMAS between the intervention and control group at 8 months follow-upThe difference in percentage of patients with an increased risk for nonadherence based on the barrier profile between the intervention and control group at 8 months follow-upThe positive and negative predictive values of the ProMAS score and the barrier profile measured at drug initiation in the control group in relation to medication adherence at 8 months follow-upDifference in medication adherence in the subgroup of patients with a follow-up period of at least 1 year after drug initiation. This in fact means to assess an effect after a longer follow-up period of at least a year analogous to the primary outcome.

The process evaluation will address the following:The barriers and facilitators in the implementation of the use of the medication-adherence tool.

These influencing factors will be discussed with all pharmacists in the intervention arm by semistructured interviews. The assessment on barriers and facilitators will be based on the Tailored Implementation for Chronic Diseases’ (TICD) checklist. This is a comprehensive, integrated checklist with 57 potential determinants of practice grouped in seven domains: guideline factors, individual health professional factors; patient factors; professional interactions; incentives and resources; capacity for organizational change; and social, political, and legal factors [14].

Patients will also be interviewed about their experiences with the medication adherence assessment and interventions. Informed consent for these interviews will be obtained. Interviews will aim at gaining a better understanding of how patients and healthcare providers have experienced the intervention in terms of effort, time investment, and benefits. The purposive patient sample size will be determined based on theoretical saturation (data collection until no new information is obtained). Therefore, data review and analysis will be done in conjunction with data collection.

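### The high-risk set used for the primary comparison is formed after allocation, under collection steps described differently for the two arms, so intention-to-treat by pharmacy does not secure its comparability

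*Protocol article*

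**What the plan says.** All references are to the protocol article.

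- **Allocation comes first.** Under Pharmacies, after the draw "the pharmacies will be informed of their assignment to either the intervention group or the control group". Under Implementation of the medication-adherence tool, "Intervention pharmacists and their pharmacy assistants will receive a three-hour training session before starting the trial".
- **The pharmacy then recruits.** Under Outline of the study procedure for patients, "when the pharmacist considers the patient eligible for participation, the patient receives a short oral introduction to the study".
- **The score comes later.** The Abstract (Methods/design) places the two assessments "between 1 and 2 weeks after the start of the medication and after 8 months".
- **The result is released by arm.** The same Outline section has the profile "sent to the electronic patient file system so that the pharmacists of the intervention practices have it available during the second dispensing appointment". For the second dispensing, "the pharmacists in the control arm do not receive the results of the medication adherence assessment from their patients"; control profiles are released only once the study is complete.
- **The completion check is described for one arm.** In that section the intervention pharmacist checks whether the assessment is done. The next step asks non-completers to complete it on a tablet in the pharmacy.
- **The score has two uses.** A score of 13 or more (ProMAS section) triggers the tailored intervention (The intervention) and defines the primary population. Under Outcomes, the primary outcome is "the difference in the medication adherence of patients with an initial high risk of nonadherence between the intervention and the control group".
- **The analysis.** Data analysis calls the primary analysis intention-to-treat, within high-risk patients. It adjusts for age, gender, diagnosis and number of medications.

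**The concern.** Randomization makes the arms comparable in what was fixed before allocation. Membership of the primary set is not fixed then. It depends on a questionnaire completed later, at pharmacies that know their arm, with follow-up of non-completers described for one arm and the result read during the trial in one arm.

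Intention-to-treat keeps each patient in the arm of their pharmacy. It cannot make comparable two subsets selected by a measurement taken after allocation. Even if the same kinds of patients were approached in both arms, the patients ending up with a score of 13 or more could differ in their underlying adherence. That difference would enter the primary estimate directly.

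The Discussion acknowledges recruitment bias and contamination through GPs, but not this route. The article states no 8-month PDC comparison between arms in all enrolled patients. The 1-year comparison is listed among outcomes based on all participants, yet it is described as analogous to the primary outcome, so its population is unclear.

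**Working it through.** **1. The plan's own figure.** Inputs from Sample size: 60% nonadherent in high-risk controls (40% adherent), a gain of 20 (read as points, so 60% adherent), ICC 0.05, power 80%, alpha 5%, 14 pharmacies. Two-sided testing and 7 pharmacies per arm are assumptions.

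- Unclustered n per arm = (1.96 + 0.842)² × (0.40×0.60 + 0.60×0.40) / 0.20² = 94.19.
- Per pharmacy, m solves 7m = 94.19 × [1 + (m − 1)×0.05], so m = 94.19×0.95 / (7 − 0.05×94.19) = 39.06. The stated 39 reproduces.
- 39 / 0.70 = 55.7, so 56. This also reproduces. The sample size is not in question here.

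**2. Standard error at the planned size.** Design effect = 1 + 38×0.05 = 2.9. Patients per arm = 7×39 = 273. With no true effect, SE = √(2×0.24×2.9/273) = 0.071.

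**3. Bias if classification shifts in one arm only.** Per 100 enrolled, the plan's figures give 40 high-risk patients, of whom 24 are nonadherent. Suppose d of the 40 intervention-arm patients fall below the cut-off, and a fraction q of those d are nonadherent. Then

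bias in favour of the intervention = 0.60 − (24 − d×q)/(40 − d).

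The values of d and q are assumptions; the documents give neither. Set size is held at 39 per pharmacy.

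| d | q | Calculation | Bias (points) | False-positive rate |
|---|---|---|---|---|
| 4 | 0.80 | 0.60 − 20.8/36 | +2.2 | 6.1% |
| 4 | 0.45 | 0.60 − 22.2/36 | −1.7 | 5.6% |
| 10 | 0.80 | 0.60 − 16/30 | +6.7 | about 15% |
| 10 | 0.45 | 0.60 − 19.5/30 | −5.0 | about 11% |

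The false-positive rate is Φ(|bias|/SE − 1.96) + Φ(−|bias|/SE − 1.96).

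**4. Comparison in all enrolled patients.** Moving a patient across the cut-off does not change who is in this comparison. Its cost is dilution.

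- If only the 40% at high risk benefit, the expected difference is 0.40×20 = 8 points.
- Evaluable patients per pharmacy = 39/0.40 = 97.5. Design effect = 1 + 96.5×0.05 = 5.825.
- Taking 50% adherence overall (the average in Background) against 58%: SE = √[(0.25 + 0.2436)×5.825/682.5] = 0.065.
- Power = Φ(0.08/0.065 − 1.96), about 23%.

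**5. Would a comparison in low-risk patients detect the shift?** With 50 of 100 nonadherent overall, 26 of the 60 low-risk patients are nonadherent (43.3%).

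- d = 10, q = 0.45: (26 + 4.5)/70 = 43.6%, a move of 0.2 points.
- d = 10, q = 0.80: (26 + 8)/70 = 48.6%, a move of 5.2 points.
- At 58.5 low-risk patients per pharmacy the design effect is 3.875 and SE 0.068. The chance of a significant result is about 5% and 12%, so the check has almost no power.

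**The case against.** **What stands against the point.** The questionnaire and cut-off are the same in both arms. The default is completion at home from a system-sent e-mail, and the score is taken before any barrier profile is discussed. Giving the result to intervention pharmacists is part of the intervention and cannot be removed. The larger biases need a quarter of high-risk patients to change class in one arm; at 4 of 40 the false-positive rate barely moves from 5%. The share scoring 13 or more by arm is ordinary baseline reporting, which an article may leave to the full plan.

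**Stronger readings that the document does not support.**

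- A reader might infer that patients answer differently because they are told different things about who reads the result. The article does not give the wording of the patient information, so this is possible but not shown.
- A reader might infer that staff watch intervention patients answer, or that only intervention patients answer in the pharmacy. Nothing says staff look on. The Outline section also offers in-pharmacy completion, with no arm named, to participants without internet at home. The tablet request follows a sentence about the intervention pharmacist, but its own wording names no arm.
- A reader might infer that everyone serving intervention patients is trained. Training covers the pharmacists and one assistant per pharmacy.
- A reader might take a difference in low-risk patients as proof of selection. It could equally be spillover from trained staff.

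**What survives.** The order of events, the arm-specific release of the result, the arm-specific completion check and the double use of the score are all in the text.

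**Conclusion.** The point holds as a risk created by the design, not as a demonstrated imbalance. The primary set is selected after allocation, by a self-report whose handling is described differently for the two arms, and the intention-to-treat label does not cover that selection. The covariates named in Data analysis include neither the baseline ProMAS score nor the mode of completion.

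Direction and size cannot be determined from the document. Under the assumed shifts, the bias is about 2 to 7 points either way, against a design effect size of 20, with a false-positive rate of about 6% to 15%. The lower end is minor; the upper end would matter for a borderline result. These figures rest on the plan's 40% high-risk share and 60% nonadherence, 7 pharmacies per arm, a two-sided test, and assumed values for how many patients change class and how adherent they are.

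**What to change.** **In Outline of the study procedure for patients:**

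- State that the completion check and the tablet request at second dispensing apply identically in both arms.
- State that both arms receive the same patient information on who sees the answers.
- Record the mode (home online, paper, pharmacy tablet) and date of completion.

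**In Data analysis:**

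- Pre-specify 8-month PDC by allocated pharmacy in all enrolled patients, whatever their score, as a supporting sensitivity analysis. Reclassification at the cut-off cannot bias it. It does not protect against arms enrolling different patients, which is why the procedure should also be harmonised.
- Report by arm the share scoring 13 or more and the baseline ProMAS distribution.
- Show any low-risk comparison descriptively only, given its low power and the spillover explanation.

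**Cost.** The primary question, sample size and intervention stay as they are. The work is a procedural clarification, two recorded items, one additional model and a short table. Control pharmacies take on the completion check if they do not already do it. The all-enrolled analysis is diluted (about 23% power for 8 points) and must not be presented as confirmatory. Trial status says recruitment was already under way, so the procedural change helps only patients still to be enrolled; the analyses apply to all.

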#### Adherence

Medication adherence is calculated as the percentage of days covered by medication (PDC) based on pharmacy dispensing of one drug group since the start of the therapy until the end of the study period. Patients with a PDC of at least 80 % are labeled as “sufficiently adherent.” PDCs are calculated per medication group (see Appendix), except for blood glucose lowering drugs. As for diabetes, often, more than one drug is used, and patients have to adhere to each drug from the subclass, e.g. to biguanides and sulfanilamide derivatives. Data on dispensing will be based on routine pharmacy data collection.

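### As written, a completion check and re-invitation at the second dispensing is given to intervention pharmacies with no control counterpart, so entry to the high-risk primary population follows different rules by arm

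*Protocol article*

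**What the plan says.** The protocol article, under Outline of the study procedure for patients, sets a common first route into the trial. Registered patients receive an email one week after the first dispensing and decide at home: "If the patient decides to participate, (s)he answers the link in the email received and completes the survey".

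The steps for the second dispensing then differ by arm.

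- Control: "the pharmacists in the control arm do not receive the results of the medication adherence assessment from their patients, and they provide usual care".
- Intervention: "The pharmacist in the intervention group checks whether the patient has completed the medication adherence assessment", and the pharmacist provides the second supply.
- Next step, no arm named: "If the patient has not completed the assessment at the moment of the second dispensing, the patient is asked whether (s)he would like to participate"; the questionnaire is then filled in on the premises, by tablet.

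The same section has one in-pharmacy route that is not tied to an arm. It is for people preferring the online form who "do not have access to a computer or Internet at home can fill out the questionnaire at the pharmacy during their visit for the second" supply.

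For the primary outcome, the Outcomes section says: "The primary outcome is the difference in the medication adherence of patients with an initial high risk of nonadherence between the intervention and the control" arm. High risk is a baseline ProMAS score of 13 or more (Measures, ProMAS). Adherence is the percentage of days covered (PDC), "based on pharmacy dispensing of one drug group since the start of the therapy until the end of the study period".

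**The concern.** A patient without a baseline ProMAS score cannot be classed as high risk and so cannot enter the primary comparison. Any step that gets more patients to complete the questionnaire is therefore a step that forms the primary population. Here that step is written for one arm.

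The extra route is also not neutral with respect to the outcome. Study design says a first supply usually lasts two weeks, so the second dispensing is the first refill. A patient re-invited at that visit has, by construction, already refilled once. A patient who enrolled at home by email need not have. Since PDC runs from the start of therapy, the first refill is part of the outcome.

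The planned analysis does not remove this. Pharmacies are told their allocation after randomization (Recruitment, Pharmacies), and patients are recruited by those pharmacies. Intention-to-treat keeps patients in the arm of their pharmacy but cannot equalise who was enrolled. The adjustment covariates under Data analysis (age, gender, diagnosis, number of medications) do not include route or timing of entry. The Discussion acknowledges recruitment bias in general, not as a difference between arms, and says the characteristics of nonresponders will not be analysed.

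**Working it through.** **1. The second dispensing, side by side**

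| Step | Intervention | Control |
|---|---|---|
| Check whether the survey is complete | Stated | Not stated |
| Re-invite non-completers | Follows directly on that check; arm not named | Not stated |
| No-internet completion in the pharmacy | Available | Available |

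The no-internet route serves people who already want to take part. It prompts no one who has not responded, so it is not a control counterpart to the re-invitation.

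**2. The plan's own figure**

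Inputs from Sample size: 40% adherent in control (60% nonadherent), a 20-point gain to 60%, intracluster correlation 0.05, power 80%, alpha 5% (two-sided assumed), 14 pharmacies (7 per arm assumed).

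- Without clustering: n = (0.24 + 0.24)(1.960 + 0.842)² / 0.20² = 94.2 per arm.
- With clustering: solving 7m = 94.2 × [1 + (m − 1) × 0.05] gives m = 39.06. The plan states 39 per pharmacy.
- At m = 39 the design effect is 1 + 38 × 0.05 = 2.90, and the effective n is 273/2.90 = 94.1 per arm.

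The stated sample size reproduces and is not affected by this point. It supplies the standard error for what follows: √(2 × 0.24/94.1) = 0.0714.

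**3. Effect of conditioning on the first refill, with no treatment effect**

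Assumptions not in the document:

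- a share q of starters does not collect a second supply, and none of them reaches PDC ≥ 80%;
- a share s of the intervention arm enters by re-invitation, with no equivalent share in control;
- re-invited patients are otherwise like those who completed on time, of whom 40% are adherent in both arms.

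Adherence among those who return is 0.40/(1 − q). The spurious difference is s × [0.40/(1 − q) − 0.40].

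| q | s | Adherence among returners | Spurious difference | Two-sided type I error |
|---|---|---|---|---|
| 10% | 20% | 0.444 | 0.20 × 0.044 = 0.9 points | 5.2% |
| 20% | 35% | 0.500 | 0.35 × 0.100 = 3.5 points | 7.8% |
| 30% | 50% | 0.571 | 0.50 × 0.171 = 8.6 points | 22.4% |

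With s between 10% and 40% over the same range of q, the difference runs from 0.4 to 6.9 points.

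**4. How easily the sign can change**

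Re-invited patients had not answered the email. If, having refilled, they are a relative q less adherent than other returners, their rate is 0.40/(1 − q) × (1 − q) = 0.40 and the difference is zero. At q = 20% that means 20% less adherent in relative terms (0.50 falls to 0.40). If they are less adherent than that, the difference favours control.

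**The case against.** The strongest objection is that the re-invitation sentence names no arm. It is a separate step, the flow diagram is not available here, and the article condenses a fuller protocol. A reader might infer that control pharmacies are barred from re-inviting; the text does not say so. What stands is narrower: the only completion check is assigned to the intervention pharmacist, the re-invitation depends on knowing its result, and no control equivalent is written. If control pharmacies do re-invite, the plan has to say so.

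A reader might also infer that intervention adherence is inflated. The documents do not support that as a net result. Selection on the refill pushes one way, selection on not answering the email may push the other, and step 4 of the working shows that a moderate offset cancels the effect.

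The inputs q and s have no source in the documents, and the formula leans upwards in two ways. It sets control entry at the second dispensing to zero, although the no-internet route is open there; only the difference in shares matters. It also applies the non-return rate of all starters to on-time completers, who had agreed to be registered, had a second appointment made and answered a survey, and whose own rate may be lower. The 22.4% type I error is the extreme corner.

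Finally, it is tempting to argue that answering in the pharmacy changes who is labelled high risk. The text says only that the survey is completed there on a tablet; it does not describe the pharmacist looking on, and nothing in the documents shows an effect on scores.

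None of this removes the difference in written entry rules.

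**Conclusion.** The point holds as a difference in how the two arms' primary populations are formed, with the extra intervention route conditioned on a component of the outcome. This can bias the primary comparison. Conditioning on the refill alone is worth roughly 1 to 9 points in favour of the intervention, and about 3.5 points in the central case, against a planned 20. Those sizes depend on the assumed q and s and on re-invited patients being otherwise like on-time completers. The documents fix neither the net size nor the net direction. The case for acting is that the rules for entering the primary analysis should be the same in both arms, and the planned analysis cannot recover that afterwards.

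**What to change.** 1. State the same second-dispensing step for both arms. The control pharmacist sees only a completed/not-completed flag, re-invites non-completers and offers completion in the pharmacy, with the score and barrier profile withheld.
2. Record the time and route of questionnaire completion for every patient (home email, paper, in-pharmacy no-internet route, re-invitation).
3. Add a sensitivity analysis of the primary outcome, limited in both arms to patients who completed the baseline questionnaire before the second dispensing.

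The cost is one extra step in control pharmacies; the registration step, by tablet or web browser, is already written for both arms. Trial status says recruitment is under way, so control patients enrolled before the change will have entered under the present procedure. The sensitivity analysis addresses this, because on-time completion at home is offered in the same way in both arms throughout.

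Making that restriction the primary analysis is less attractive. Under the assumed range it would remove 20-50% of intervention patients, and it would also drop no-internet participants and late postal returns in both arms, cutting into the 39 per pharmacy the power calculation needs.
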